### Sample size

With 107 in M-CT versus in TAU 107 participants per condition the trial will be powered to detect a difference of 20% in the cumulative incidence rate of relapse/recurrence with a 2 year follow-up in a 2-tailed test at the conventional alpha level of 0.05 and a power of (1-beta) = 0.80, while conservatively assuming that relapse/recurrence will occur in 50% of the cases. Allowing for a drop-out of 20% we need to include 268 participants at baseline.

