### Analysis

Cox regression analysis (survival analysis) will be performed, including as covariates the stratification variables that will be used in randomization, i.e.: number of previous episodes and type of care (primary/secondary/no care). Analysis will be conducted by intention to treat, including all subjects randomized in the study, and per protocol, including only subjects satisfying protocol. Statistical significance will be set at *P *< .05.

Mixed-model analysis of variance (ANOVA) will be used for the other variables, including baseline values of the dependent variable as a covariate in all analyses. We shall use implicit and explicit cognitive measures and stress measures (daily hassles) to explore the extent to which they mediate relapse and recurrence during treatment and follow up.

For the economic evaluation the balance between costs and health outcomes will be compared across strategies using a societal perspective. Primary outcome measure: the number of depression-free days. Both short-term and long-term consequences will be compared. Additionally, Quality Adjusted Life Years will be used as outcome (see also Table 1).

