The economic evaluation will be conducted both as a cost-effectiveness analysis with depression-free survival time as the clinical end term, and as a cost-utility analysis with incremental costs per quality adjusted life years (QALYs) gained as the clinical endpoint. For the latter, health-related quality of life, will be assessed with help of the EQ-5 D at baseline and follow-ups. Direct medical and direct non-medical cost data are collected with the TIC-P [22], a widely used health service receipt interview in economic evaluations. Unit resource use (GP visits, hospital days, etc.) will be multiplied by their appropriate integral cost prices [41]. Indirect non-medical cost data related to production losses through work loss days and work cutback days will be sampled with specific modules of TIC-P [22]. For the economic evaluation use will be made of the pertinent guidelines [42-44]. In other words, analyses will be conducted in agreement with the intention-to-treat principle, the societal perspective will be taken encompassing intervention costs, direct medical costs, direct non-medical costs and indirect costs. The latter will encompass production losses due to absenteeism and due to working less efficient while at work. Production losses will be economically valuated using the friction cost method [45] as per the Dutch guideline [42]. The time horizon will be set at two years and therefore costs and effects will be discounted. Costs and effects will be analyzed simultaneously, incremental cost-effectiveness ratios (ICERs) will be calculated and placed within 95% confidence intervals, 2,500 bootstrap replications of the ICERs will be projected on a cost-effectiveness plane, ICER acceptability curves will be plotted against different willingness-to-pay ceilings and sensitivity analysis will be conducted as a matter of course focusing on uncertainty in the analysis.

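### The economic analysis specifies no baseline adjustment for incremental QALYs or costs, although EQ-5D and TIC-P are both collected at T0; adding it would gain precision at no cost in data

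*Protocol article*

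**What the plan says.** Appendix 1 (Statistical Analysis Plan) sets out two economic analyses, one on depression-free survival time and one on QALYs. The Analysis section makes depression-free days the primary economic outcome and QALYs an additional one.

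On quality of life, the appendix says "health-related quality of life, will be assessed with help of the EQ-5 D at baseline and follow-ups". Table 1 schedules EQ-5D and TIC-P at T0, at 3 months and every three months from then to 24 months. The economic paragraph plans ICERs with 95% confidence intervals, "2,500 bootstrap replications of the ICERs" shown on a cost-effectiveness plane, acceptability curves and sensitivity analyses, and it relies on cited guidelines. It names no covariate for the incremental cost or the incremental effect.

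The clinical analyses do name covariates. The Cox model includes the stratification factors (Analysis; Appendix 1). The mixed models for the other outcomes are specified as "including baseline values of the dependent variable as a covariate in all analyses". A net benefit regression on baseline characteristics is also planned in Appendix 1, but its purpose is to find subgroups in which the intervention is especially cost-effective. It does not supply the overall adjusted increment.

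**The concern.** A QALY total is the area under a utility curve that begins at the baseline value, and later utilities tend to follow the baseline value. Two-year costs likewise tend to follow prior resource use. If the increments in each bootstrap replicate are raw mean differences, a chance baseline difference in utility or resource use is partly carried into the increments. The between-patient variation that baseline could explain also stays in the standard error.

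The trial is sized for relapse or recurrence and not for costs or QALYs, so precision in the economic comparison is worth having. The appendix is otherwise quite specific on the economic side: it gives the number of replications, the perspective, the horizon, the friction cost method and discounting. As it stands, a raw or an adjusted increment would both comply, and the choice could be made after the data are seen.

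**Working it through.** **1. The plan's own figure, as the source of n.** The Sample size section gives: "With 107 in M-CT versus in TAU 107 participants per condition"; "a difference of 20% in the cumulative incidence rate of relapse/recurrence with a 2 year follow-up"; "conservatively assuming that relapse/recurrence will occur in 50% of the cases"; "in a 2-tailed test at the conventional alpha level of 0.05"; "a power of (1-beta) = 0.80". Reading 50% as the average of the two arms (60% versus 40%):

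- Without continuity correction: n = [1.96 × √(2 × 0.5 × 0.5) + 0.8416 × √(0.6 × 0.4 + 0.4 × 0.6)]² / 0.2² = (1.3859 + 0.5831)² / 0.04 = 96.9, so 97 per arm.
- With continuity correction: n' = (96.9 / 4) × [1 + √(1 + 4 / (96.9 × 0.2))]² = 106.7, so 107 per arm.
- Drop-out: 214 / 0.8 = 267.5, so 268.

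Both stated figures reproduce, and this point disputes neither. Below, n = 107 per arm is used; 134 per arm (268 / 2) would apply if everyone randomised were analysed.

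**2. Size of a chance baseline utility difference.** The documents give no EQ-5D SD, so 0.15 to 0.25 is assumed. SE = SD × √(2/n).

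| Assumed SD | SE, n = 107 | 1.96 SE, n = 107 | SE, n = 134 |
|---|---|---|---|
| 0.15 | 0.0205 | 0.040 | 0.0183 |
| 0.20 | 0.0273 | 0.054 | 0.0244 |
| 0.25 | 0.0342 | 0.067 | 0.0305 |

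**3. How much of it reaches the QALY difference.** The first EQ-5D interval is three months, so by the trapezoid rule the baseline value has weight 0.5 × 0.25 = 0.125 years. That is 0.125 / 2 = 6.25% of the two-year area.

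- Direct part at 1.96 SE: 0.125 × 0.040 = 0.005 to 0.125 × 0.067 = 0.008 QALY.
- With carry-over: let b be the slope of the two-year average utility on baseline, assumed 0.3 to 0.7. The shift is 2 × b × imbalance. At 1.96 SE this runs from 2 × 0.3 × 0.0402 = 0.024 to 2 × 0.7 × 0.067 = 0.094 QALY.

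The pass-through is therefore partial, and most of it depends on the assumed slope.

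**4. Gain from adjustment.** With baseline-outcome correlation ρ (assumed), adjustment multiplies the variance of the increment by 1 − ρ².

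| ρ | Variance factor | SE factor | Equivalent sample, 1/(1 − ρ²) |
|---|---|---|---|
| 0.3 | 0.91 | 0.95 | 1.10 |
| 0.5 | 0.75 | 0.87 | 1.33 |
| 0.7 | 0.51 | 0.71 | 1.96 |

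The same factor applies to costs, with ρ the correlation between T0 cost and two-year cost. No cost SD or correlation is given, so no euro figure is offered.

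**5. Is the unadjusted contrast valid?** A simulation was run with 5,000 trials, 107 per arm, normal outcomes and no missing data. Bias was about 0 with and without adjustment. Coverage of the 95% interval at ρ = 0.3, 0.5 and 0.7 was 0.949, 0.945 and 0.957 unadjusted, against 0.949, 0.950 and 0.953 adjusted. The spread of the estimates fell from 0.138 to 0.132, from 0.139 to 0.120 and from 0.135 to 0.096, ratios of 0.96, 0.86 and 0.71, in line with step 4.

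**The case against.** The strongest reply is that this reads silence as a plan. No sentence says the increments are unadjusted. Bootstrapping is compatible with raw or regression-based increments, the economic methods are referred to guidelines that are not shown, and a journal article may leave the covariate set to a fuller plan. That stands. A reader might infer from the economic paragraph that an unadjusted analysis has been decided; the text supports only that no baseline adjustment is specified.

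Three further replies also stand.

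- A reader might infer that chance imbalance passes straight through and invalidates the result. It does not: baseline carries only 6.25% of the area directly, and the interval of a randomised comparison already allows for chance imbalance, as the coverage figures show.
- A reader might infer that the cost-effectiveness conclusion rests on the QALY difference. The Analysis section puts depression-free days first, and that outcome contains no baseline EQ-5D term.
- The documents give no expected QALY effect, so the shift in step 3 cannot be called large or small against the treatment effect.

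What these replies do not remove is the gain. The mixed-model sentence on baseline values is not expressly extended to the economic evaluation, the net benefit regression serves another question, and the baseline data are already being collected.

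**Conclusion.** The point holds as a free improvement and not as an error. The economic analysis describes bootstrapped ICERs and specifies no adjustment for baseline utility or baseline cost, while the clinical analyses do name baseline values and stratification factors.

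Unadjusted increments would be unbiased with valid intervals under randomisation. They would be less precise, and exposed to whatever imbalance the realised sample happens to have. At an assumed correlation of 0.3 to 0.7, adjustment multiplies the standard error of an increment by about 0.95 to 0.71.

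The effect side of the point is limited to the cost-utility analysis; the cost side applies to both economic analyses. The size rests wholly on assumed SDs, slopes and correlations. The simulation used normal, complete data, so it does not speak to skewed costs or to the 20% drop-out that the plan allows for.

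**What to change.** Add wording to the economic paragraph of Appendix 1 to this effect:

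- Within each bootstrap replicate, incremental costs and QALYs are estimated jointly by regression (for example seemingly unrelated regression) on treatment, the stratification factors, baseline EQ-5D utility and baseline TIC-P cost.
- These adjusted increments are used for the ICER, the cost-effectiveness plane and the acceptability curves.
- In the analysis on depression-free days, the effect is adjusted for the stratification factors, and costs are adjusted for baseline TIC-P cost.

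The cost is a sentence or two of text and a little analysis code. No new data, visits or participants are needed, and the sample size does not change. The wording should be fixed before outcome data are seen, so that adjustment is not chosen afterwards.

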## Trial objectives and Purpose

In this study, the addition of an internet based intervention with automated tele-monitoring (Mobile-CT, referred to as M-CT) to TAU, will be compared to TAU alone in a sample size of 214 (2x107) recovered patients. Alongside the randomized controlled trial, a cost effectiveness analysis (from a societal perspective) will be conducted.

It is hypothesized that adding M-CT is clinically superior to treatment-as-usual alone (TAU) for preventing relapse and recurrence in depressive disorder. In addition, we expect that the intervention dominates the comparator condition in terms of cost-effectiveness. Since co-morbidity with concurrent chronic somatic illnesses, is defined by the American Psychiatric Association [10] as a risk factor for future relapse and recurrence, differential response in this group of patients will be examined explicitly. We will also conduct moderator analysis to see if there are any baseline characteristics of the participants that are prognostically relevant for treatment response. Finally, we will conduct incremental cost-benefit regression analysis to identify subgroups where the intervention is particularly cost-effective.

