## Appendix 1: Statistical Analysis Plan

All analysis will be conducted in agreement with the intention to treat principle as per the CONSORT statement. Cox regression analysis will be performed, including as covariates the stratification variables that will be used in randomization, i.e.: number of previous episodes, type of care (no/primary/secondary). Statistical significance will be set at P < .05. When adding the intervention to TAU is superior then the relapse/recurrence rate in this condition should be smaller than in the comparator condition (TAU alone). Therefore, we will obtain cumulative relapse/recurrence hazard rate ratios (Hr's). To gauge the robustness of the outcomes, the above analyses will be repeated under a completers-only framework.

Since co-morbidity with a concurrent chronic somatic illness for which medical attention is received is defined by the American Psychiatric Association as risk factor for future relapse and recurrence [10], differential response in this group of patients will be examined explicitly. Subgroups that show particularly good response to the intervention will be identified by regressing SCID depression severity on the interaction term of treatment and clinical characteristics of the participants as measured at baseline. Examples of other characteristics are number of previous depressive episodes, age at which the first depression occurred, concurrent personality disorders, concurrent anxiety disorder, experienced life events, some demographic characteristics (like gender) and sense of mastery. In addition, moderator analysis will also be conducted for demographic variables such as gender, age, educational level, partner status, employment status. These variables have been shown to be of prognostic value in depressive disorder. The same set of predictor variables will also be used in an incremental net benefit regression analysis to addresses the research question in what groups the intervention is likely to be particularly cost-effective.

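### The cost-effectiveness analysis has two unreconciled effect measures, and it plans a 95% CI on an ICER that cannot be ordered under the dominance the protocol expects

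*Protocol article*

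**What the plan says.** Three places in the Protocol article bear on this.

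- **Analysis section.** For the economic evaluation: "Primary outcome measure: the number of depression-free days". QALYs are an additional outcome.
- **Appendix 1.** The evaluation is to be a "cost-effectiveness analysis with depression-free survival time as the clinical end term" and also a "cost-utility analysis with incremental costs per quality adjusted life years (QALYs) gained as the clinical endpoint". The horizon is two years, with costs and effects both discounted. On uncertainty: "incremental cost-effectiveness ratios (ICERs) will be calculated and placed within 95% confidence intervals". The results of 2,500 bootstraps are then to be displayed on the plane of cost against effect. For the decision threshold, the plan is that "ICER acceptability curves will be plotted against different willingness-to-pay ceilings". Sensitivity analysis is added. An "incremental net benefit regression analysis" is planned too, but only to find subgroups in which the intervention is particularly cost-effective.
- **Trial objectives and Purpose.** The expected result is stated: "we expect that the intervention dominates the comparator condition in terms of cost-effectiveness".

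Neither depression-free days nor depression-free survival time is defined, and neither is linked to the other. QALYs have the same supplementary role in both places, so they do not explain the difference.

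**The concern.** **Effect measure.** Both terms can be counted in days, so an ICER on either could carry the same label, cost per depression-free day gained. They are different quantities as soon as a relapse remits. The protocol allows for that, because the number of relapses is a secondary outcome. If the choice stays open, two analysts following two parts of the same article would divide the same cost difference by different effects. The choice could also be made after the data are seen.

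**Interval on the ratio.** Dominance means more effect at lower cost, hence a negative ICER. Among negative ratios, size does not track merit, and the sign alone does not separate a dominant intervention from a dominated one. A lower and an upper limit then do not mark worse and better results. This arises in the very outcome that the protocol predicts.

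**Working it through.** The economic evaluation states no ICER, power or sample size of its own, so it has no figure to reproduce. The trial's sample size was checked only to see how its 50% relapse assumption is meant. Taking 50% as the average of the two arms (60% versus 40%), two-sided alpha 0.05 and power 0.80:

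- n = [1.96·√(2·0.5·0.5) + 0.8416·√(0.24+0.24)]² / 0.2² = 96.9 per arm
- with continuity correction, (96.9/4)·[1+√(1+4/(96.9·0.2))]² = 106.7, so 107
- 214/0.8 = 267.5, so 268

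The stated 107 and 268 reproduce, and nothing below changes them.

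**1. How far apart the two measures are**

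From the documents: a 730-day horizon and a 20-point difference in relapse. Assumed: 50% versus 30% two-year relapse, a constant hazard that is the same after each recovery, and a fixed episode length D.

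One patient: relapse at day 180 with a 120-day episode and no further relapse gives 180 days of depression-free survival, but 730 − 120 = 610 depression-free days.

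By arm, with λ = −ln(1−p)/730 and mean survival time within 730 days = p/λ:

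- 50% relapse: λ = 0.000950, mean 526.6 days
- 30% relapse: λ = 0.000489, mean 614.0 days
- gain in depression-free survival = 614.0 − 526.6 = 87.4 days

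For depression-free days, the probability u(t) of being well follows u′(t) = −λu(t) + λu(t−D), with the last term zero for t < D. Its integral over 730 days gives the expected well days.

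| Episode length D (days) | 30% arm | 50% arm | Gain in depression-free days | 87.4 / gain |
|---|---|---|---|---|
| 60 | 710.0 | 692.2 | 17.9 | 4.9 |
| 90 | 701.1 | 675.8 | 25.3 | 3.5 |
| 180 | 677.7 | 634.7 | 43.0 | 2.0 |
| 365 | 642.9 | 577.0 | 66.0 | 1.3 |

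For a given cost difference, the ICER changes by the factor in the last column. With 60% versus 40% instead, the same calculation gives a survival gain of 93.6 days against 20.9, 29.2, 48.3 and 71.0 depression-free days, so factors of 4.5, 3.2, 1.9 and 1.3.

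**2. Why an interval on the ICER cannot be ordered**

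ICER = ΔC/ΔE, with invented amounts:

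- saves 1,000, gains 20 days: −1,000/20 = −50 (dominant)
- saves 1,000, gains 40 days: −1,000/40 = −25 (dominant and better, yet less negative)
- costs 1,000 more, loses 20 days: 1,000/(−20) = −50 (dominated)

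To see the effect on an interval, 2,500 independent normal draws of ΔE (days) and ΔC (euros) stood in for the bootstrap. All means and standard errors are assumed, as is the willingness to pay of EUR 20 per depression-free day. The percentile limits are illustrative only.

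| | ΔE (SE) | ΔC (SE) | More effect, cheaper | More effect, dearer | Less effect, cheaper | Less effect, dearer | 2.5 to 97.5 percentile of ICER |
|---|---|---|---|---|---|---|---|
| A | 60 (20) | −1,000 (400) | 99% | 1% | <1% | 0% | −51 to −3 |
| B | 40 (40) | −500 (2,000) | 51% | 33% | 9% | 7% | −391 to 343 |

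In A almost every draw is dominant, yet neither −51 nor −3 is the better end: a ratio near zero can come from a small saving or from a large health gain. In B the range mixes dominant, dominated and trade-off results.

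Incremental net benefit is 20·ΔE − ΔC, with SE = √[(20·SE_E)² + SE_C²]:

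- A: 1,200 + 1,000 = 2,200; SE = √(400² + 400²) = 566; 95% CI 1,091 to 3,309
- B: 800 + 500 = 1,300; SE = √(800² + 2,000²) = 2,154; 95% CI −2,922 to 5,522

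Both intervals run from worse to better and can be read directly.

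**The case against.** The strongest reply is that Appendix 1 already plans most of what is needed. The plane shows where the replicates fall, and an acceptability curve is the probability of positive net benefit at each ceiling. This stands, and it limits the harm. A reader might infer that dominance could not be judged at all. The documents do not support that, because the interval is not reported alone and nothing makes it the decision criterion.

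A second reply is that no interval method is stated, and a condensed article may leave that to a fuller plan. Also correct: a reader might infer a percentile interval, but the text does not say so. The point does not depend on it, since the lack of order belongs to the ratio scale and affects any interval read on that scale.

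Third, a reader might infer that costs and effects would cover different periods if survival time is used. Appendix 1 sets one two-year horizon for both. Time to first relapse, censored at 24 months, lies within it; leaving out later well days is a choice of outcome, not a mismatch of periods.

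Fourth, the two terms might be meant as synonyms, and ending survival time at the first relapse is the ordinary reading, not a stated definition. But the article nowhere equates them, and they part company once a relapse remits.

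Finally, all costs, standard errors and episode lengths here are assumed, and scenario A shows that replicates need not scatter. That bears on size, not on the inconsistency or on the ordering problem, which is present in A as well.

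**Conclusion.** The point stands in two parts. First, the article gives the cost-effectiveness analysis two effect measures that it does not reconcile. The incremental effect, and so the ICER, can differ by a factor of about 1.3 (365-day episodes) to 4.9 (60-day episodes), given 50% versus 30% relapse, a constant hazard and survival time ending at the first relapse. Second, a 95% CI on the ICER is not interpretable if replicates are dominant, as the protocol expects, or span quadrants.

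This should be corrected, but its reach is limited. The QALY analysis is a legitimate second evaluation and is no part of the conflict over effect measures, although any CI on its ICER has the same ordering problem. The primary clinical analysis and the sample size of 268 are not touched.

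**What to change.** 1. Name and define one effect measure in both the Analysis section and Appendix 1. Depression-free days over the full two-year horizon agrees with the Analysis section. If time to first relapse is kept in the economic evaluation, label it a secondary effect measure.
2. Report the ICER as a point estimate, with the share of bootstrap replicates in each quadrant and separate 95% CIs for incremental cost and incremental effect.
3. Put the 95% CI on incremental net benefit at stated willingness-to-pay values, alongside the acceptability curves. The same 2,500 bootstraps serve, and the net benefit approach already planned for subgroups extends to the main comparison.

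The cost is a little analysis wording, with no new data collection. The one practical burden is that counting depression-free days requires episode end dates, which must be taken from the SCID interviews at 3, 12 and 24 months and hence dated in retrospect.
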